# Rationale and design of randomized non-inferiority clinical trial to compare the safety and efficacy of ticagrelor monotherapy with dual antiplatelet therapy in chronic coronary syndrome patients post percutaneous coronary intervention (TICALONE-TAHA10 Protocol)

**DOI:** 10.1371/journal.pone.0325663

**Published:** 2025-07-16

## Abstract

**Background:**

Despite the wide variety of antiplatelet regimens and durations, the optimal treatment approach for chronic coronary syndrome (CCS) patients remains a subject of ongoing debate. While current guidelines recommend dual antiplatelet therapy (DAPT) with aspirin and clopidogrel, the development of drug-eluting stents (DES) and more potent agents has sparked interest in shorter DAPT regimens, followed by P2Y12 inhibitor monotherapy, as a potential alternative. Recent trials and meta-analyses have shown that this approach may provide similar protection against thrombotic events with reduced bleeding risk. Despite promising data, the safety and efficacy of Ticagrelor monotherapy specifically in CCS patients have not been rigorously tested in randomized trials.

**Methods:**

TICALONE is a non-inferiority, two-arm, double-blinded, randomized controlled clinical trial designed to evaluate the safety and efficacy of ticagrelor monotherapy compared to DAPT in CCS patients following PCI. Eligible patients undergoing PCI with drug-eluting stents will be randomly assigned to receive either conventional DAPT (aspirin and clopidogrel) or ticagrelor monotherapy for six months. Follow-up visits will be conducted at 1, 3, 6, and 12 months post-PCI to assess efficacy and safety endpoints. The primary efficacy endpoint is a composite endpoint of cardiac death, myocardial infarction, stroke, stent thrombosis, and the need for revascularization. The primary safety endpoint is the occurrence of Bleeding Academic Research Consortium (BARC) type 3 or 5 bleeding events. The secondary endpoints include components of the primary efficacy endpoint, any bleeding event (BARC type 1–5), and all-cause mortality. Ancillary endpoints are other adverse events including dyspnea, drug adherence, and reaction. All endpoints will be monitored by a Data Safety Monitoring Board (DSMB) and Trial Management Committee (TMC). Statistical analysis and reporting of trial results will follow the estimand framework. Kaplan-Meier estimates will be used to assess event rates, while the log-rank test and Cox regression analysis will be employed to compare safety and efficacy outcomes between the groups.

**Discussion:**

This trial may serve as a crucial step toward eliminating aspirin from post-PCI regimens, specifically in CCS patients. By comparing the safety and efficacy of Ticagrelor monotherapy with the conventional DAPT regimen and addressing potential risks of aspirin-free therapy and adverse events like dyspnea, this study could offer valuable insights into the possibility of P2Y12 monotherapy’s safe adoption in this population.

**Trial registration:**

TICALONE is registered at https://clinicaltrials.gov/ with the identifier NCT06509893.

## Introduction

### Background and rationale

The optimal antiplatelet therapy for patients with chronic coronary syndrome (CCS) undergoing percutaneous coronary intervention (PCI) remains uncertain. Current guidelines recommend dual antiplatelet therapy (DAPT) consisting of aspirin and clopidogrel, a P2Y12 inhibitor, for at least 6 months post-PCI, followed by antiplatelet monotherapy [1,2]. The development of antithrombotic stents, combined with the fact that ischemic risk is highest in the acute post-PCI phases and declines over time while bleeding risk remains constant, has made regimens focusing on bleeding risk more appealing. On the other hand, while DAPT reduces the risk of stent thrombosis and recurrent ischemic events, its use is associated with a significantly higher risk of bleeding compared with single antiplatelet therapy without antithrombotic benefits [3]. These considerations, along with the well-known gastrointestinal toxicity linked to aspirin, have questioned the necessity of maintaining aspirin beyond the acute post-PCI phase and made the background to develop clinical trials such as GLOBAL-LEADERS, ULTIMATE-DAPT, TWILIGHT, STOPDAPT-2, TICO and T-PASS with the aim to explore the safety and efficacy of P2Y12 inhibitor monotherapy following a short course of DAPT [4–7]. These studies have shown that shorter DAPT regimens may offer similar protection against thrombotic events while significantly reducing the risk of bleeding [8–11]. While evidence highlights the need for caution in the early discontinuation of aspirin, particularly in high-risk patients such as those with acute coronary syndrome (ACS), ASET studies have suggested that completely omitting aspirin from the regimen (aspirin-free regimen) and administering P2Y12 inhibitor (prasugrel) monotherapy following PCI is not associated with any stent thrombosis in patients with CCS [12,13]. This non-inferiority of immediate prasugrel monotherapy compared to DAPT for cardiovascular events was also demonstrated in STOPDAPT-3 [14].

Although the safety and feasibility of prasugrel monotherapy in ASET-JAPAN and ASET studies were demonstrated, STOPDAPT-3 showed that prasugrel monotherapy is not superior to DAPT for preventing bleeding in ACS or high-risk bleeding patients [13–15]. Moreover, Ticagrelor monotherapy, following 3 months of DAPT, demonstrated a 44% reduction in Bleeding Academic Research Consortium (BARC) 2–5 bleeding, with no observed difference in major adverse cardiovascular events (MACE) between the groups of high-risk patients [16]. This potent and reversible P2Y12 inhibitor, provides more consistent and rapid platelet inhibition compared to clopidogrel, resulting in a stronger anti-thrombotic effect [17]. Additionally, The PLATO trial showed a 16% reduction in MACE with Ticagrelor compared to Clopidogrel in ACS patients on a DAPT regimen, primarily due to a decrease in myocardial infarctions and cardiovascular deaths during the 1-year follow-up period [18]. On the other hand, the 90 mg twice-daily dose of ticagrelor carries a similar major bleeding risk to that of clopidogrel [19,20]. These findings suggest that ticagrelor may be a better choice for aspirin-free regimens following PCI. However, the safety and efficacy of immediate ticagrelor monotherapy in patients with CCS undergoing PCI have not yet been rigorously evaluated in randomized controlled trials.

### Objective

Building on the background presented, we designed a randomized, two-arm, double-blinded trial aims to compare the safety and efficacy of **TICA**gre**L**or m**ON**otherapy versus DAPT in CCS patients post percutaneous coronary int**E**rvention (TICALONE). We hypothesize that immediate ticagrelor monotherapy (without the DAPT period) will be non-inferior to the conventional DAPT regimen and will provide comparable protection against ischemic events while offering a reduced bleeding risk. If confirmed, this study could influence future clinical guidelines and shift the current paradigm in post-PCI management for CCS patients. The TICALONE protocol was developed through the coordination of the [name] Clinic team and the **T**raditional and **A**dvanced **H**eart **A**pproaches clinical center, as their 10^th^ trial (TICALONE-TAHA10). It has been prepared in accordance with the guidelines outlined by the Standard Protocol Items: Recommendations for Interventional Trials (SPIRIT).

## Methods

### Study design and setting

This study is a monocentric, two-arm, double-blinded, non-inferiority, parallel, randomized, controlled clinical trial which will be conducted in [name] Clinic located in Shiraz, southern Iran to evaluate the safety and efficacy of ticagrelor monotherapy in CCS patients following PCI. This clinic is well-suited for this research due to the high volume of CCS patients referred from primary care centers and other clinics for angiography and subsequent PCI procedures.

### Participants and eligibility criteria

Given the critical need for intensive patient control and monitoring, we have established strict inclusion and exclusion criteria. Detailed inclusion and exclusion criteria are detailed below.

Inclusion criteria:

iMale or female above 20 years of age undergoing PCI with a drug-eluting stent for chronic coronary syndromeiiprovided written informed consent, as approved by the ethics committee of the Shiraz University of Medical Sciences.

Exclusion criteria:

iContraindication to aspirin, clopidogrel, ticagrelor, or any other reason that study drug should not be administered (including hypersensitivity, moderate or severe liver disease, active bleeding, and major surgery within 30 days)iiAtrial fibrillation or other indication for oral anticoagulant therapy.iiiConcomitant oral or IV therapy with strong CYP3A inhibitors, CYP3A substrates with narrow therapeutic indices (cyclosporine, and quinidine), or strong CYP3A inducers (rifampin, rifampicin, phenytoin, and carbamazepine)ivFemales of childbearing age unless negative pregnancy test at screening and willing to use effective contraception for the duration of trialvFemales who are breastfeeding at the time of enrolment.viUnsuccessful PCI or PCI without optimal stent placement; this decision is made by the supervising interventional cardiologist.viiPatients with planned surgical intervention to treat any cardiac or non-cardiac condition.viiiPrevious PCI in the last 6 months.ixCurrent (same hospitalization) or previous (within 12 months) acute coronary syndrome.xHistory of definite stent thrombosis.xiConcomitant cardiac valve disease requiring invasive therapy.xiiAcute heart failure.xiiiActive myocarditis.xivCardiomyopathy.xvPatient in hemodialysis.xviHistory of stroke or transient ischemic cerebrovascular accident.xviiHistory of intracranial hemorrhage or other intracranial pathology associated with increased bleeding risk.xviiiHemoglobin <10 g/dLxixPeptic ulceration documented by endoscopy within the last 3 months unless healing proven by repeat endoscopy.xxAny other condition deemed by the investigator to place the patient at excessive risk of bleeding with ticagrelor.xxiParticipation in another trial with an investigational drug or device.xxiiAssessment that the subject is not likely to comply with the study procedures or have complete follow-up.xxiiiKnown drug or alcohol dependence within the past 12 months as judged by the investigator.

Given that a substantial number of patients with CCS may already be on aspirin or P2Y12 inhibitors, and to enhance the applicability of the study to real-world clinical practice for this population, prior use of these agents was not included in the exclusion criteria. However, in such cases, any ongoing aspirin or P2Y12 inhibitor therapy will be discontinued upon enrollment, and the allocated study treatment will be initiated according to the assigned group protocol.

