### Intervention

An interventional cardiologist will perform angiography under the supervision of a senior interventional cardiologist. CCS patients who require revascularization based on the newest guideline [21] will undergo PCI using DES. FFR (Fractional Flow Reserve) ≤ 0.8 or iFR (Instantaneous Wave-Free Ratio) ≤ 0.89 will be considered as evidence of ischemia. PCI will be performed using the radial or femoral approach to achieve complete revascularization of at least one stenosis. All target lesions will be revascularized using the 4th generation DES. Randomization will take place after diagnostic angiography but before stent insertion (Fig 1). Eligible patients will be divided into two groups: the control group, which will get conventional DAPT with aspirin and Clopidogrel (80 mg aspirin once daily, and 75 mg clopidogrel once daily), and the experimental group, which will receive ticagrelor monotherapy (90 mg twice daily) following PCI for six months. Antiplatelet therapy will start before or at the time of PCI. Patients will receive a loading dose of assigned drugs (325 mg for aspirin, 300 mg for clopidogrel, and 180 mg for ticagrelor) before stent insertion unless they are already on pre-PCI maintenance therapy with the mentioned drugs. Peri-procedural aspirin use will not be allowed in the experimental arm.

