### Participant timeline

After a clear decision to conduct diagnostic angiography for CCS patients based on current guidelines [22,23]. They will be informed about the study and available options. After providing the informed consent, the pre-PCI questionnaire will be completed by an interventional cardiologist and a member of TMC. Patients will be randomized to treatment or control group after diagnostic angiography and before stent insertion. The loading dose of the assigned medications for each group will be administered to the patient prior to stent insertion. After the procedure, the enrolled patients will be visited for evaluation and management of underlying diseases, routine assessments, and optimal medical therapy. Clinical follow-ups will be performed at 1, 3, 6, and 12 months and telephone contacts will be performed every month till the end of the study. An assessment of angina status, cardiovascular drug use, dyspnea, and any serious adverse events will be recorded during these clinical follow-up visits. Illustrative participant timeline is shown in Figs 1 and 2.

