### Randomization (sequence generation, concealment, implementation)

Participants will be randomly allocated to either the control group or the experimental group in a 1:1 ratio using permuted block randomization through a web-based randomization service (https://www.sealedenvelope.com/randomisation/simulation/). Allocation concealment will be ensured as the randomization service will not be accessed by the interventional cardiologist until the patient has been recruited into the trial. Recruitment occurs after diagnostic angiography and before stent insertion. The only person who is involved in randomization is the interventional cardiologist who conducts PCI.

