### Blinding

The allocation of patients to each group is known only to the cardiologist responsible for randomization. This cardiologist is not involved in the patient’s treatment, follow-up, outcome assessment, or data analysis to ensure blinding of the physician team to the allocation. The allocation is stored using a code number in a computer-based data system, which will remain blinded until the analysis is complete. Neither the patients, investigators, nor data analysts will be aware of the group assignment. To ensure the blinding of participants and prevent them from identifying their assigned treatment group, despite differences in the type and number of medications, a standardized method of tablet administration was employed. Following randomization and prior to stent insertion, all patients will receive two unmarked tablets as a loading dose. In the control group, patients will be administered one 325 mg aspirin tablet and one 300 mg clopidogrel tablet. In contrast, patients in the intervention group will receive two 90 mg ticagrelor tablets, administered by the cardiologist responsible for the randomization process. For the maintenance dose, each patient will be provided with two boxes of tablets and instructed to take one tablet from each box daily, one in the morning (8:00 AM) and one in the evening (8:00 PM). In the intervention group, both boxes will contain 90 mg ticagrelor tablets, whereas in the control group, one box will contain 80 mg ASA tablets and the other will contain 75 mg clopidogrel tablets. The same cardiologist responsible for randomization will also distribute the medication boxes containing the required drugs for the six-month follow-up period. This approach is designed to preserve the double-blind nature of the study, ensuring that participants, physicians, outcome assessors, and other study personnel remain unaware of group allocations. In the event of adverse reactions or if a medication switch is deemed necessary by the DSMB or TMC, the group allocation will be unblinded, and appropriate adjustments will be made.

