### Statistical analysis

Continuous variables will be presented as mean ± SD and categorical variables will be presented as counts and percentages. The comparison of categorical variables will be conducted using either the χ² test or Fisher’s exact test. To compare continuous variables, the Student’s t-test or the Wilcoxon rank-sum test will be used for non-normally distributed data. The statistical analyses will be carried out using Stata version 18.0 (StataCorp LLC, College Station, Texas, USA). All primary and secondary endpoints will be analyzed both on an intention-to-treat basis, determined by allocation. Cumulative event rates will be estimated with the Kaplan-Meier method. The Cox log-rank approach will be utilized to compare the incidence of endpoints, specifically focusing on the time-to-first-event analyses. Patients lost to follow-up will be censored at the time of the last known contact. The null hypothesis will be evaluated on the intention-to-treat population using inferiority statistics. If the upper limit of the one-sided 95% confidence interval of the difference is less than the prespecified non-inferiority margin of 1%, ticagrelor monotherapy will be considered non-inferior to the conventional 6-month DAPT regimen. A subgroup analysis will be conducted for clinically relevant factors such as age, sex, comorbidities, prior use of aspirin or P2Y12 inhibitors, lesion or procedural characteristics, and other risk indicators. A two-sided test will be used for all hypotheses testing at a 5% significance level. The results of this study will be reported in accordance with CONSORT statement. Statistical analysis and reporting of trial results will follow the estimand framework [24].

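### Exclusion vi (unsuccessful or suboptimal PCI) can be judged only after randomisation and loading, so applying it as written conflicts with the intention-to-treat analysis

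*Protocol article*

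**What the plan says.** In Participants and eligibility criteria, item vi of the exclusion list covers an unsuccessful PCI or a stent that is not optimally placed. No objective definition is given; instead, "this decision is made by the supervising interventional cardiologist".

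Four sections fix the order of events:

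- Intervention: "Randomization will take place after diagnostic angiography but before stent insertion".
- Participant timeline: "Patients will be randomized to treatment or control group after diagnostic angiography and before stent insertion".
- Randomization: "Recruitment occurs after diagnostic angiography and before stent insertion".
- Blinding: "Following randomization and prior to stent insertion, all patients will receive two unmarked tablets as a loading dose".

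Statistical analysis says that primary and secondary endpoints are analysed by intention to treat according to allocation, and adds: "The null hypothesis will be evaluated on the intention-to-treat population using inferiority statistics". No modified population is defined. Treatment of missing values deals with loss to follow-up and medication switches, not with patients who turn out to meet criterion vi. The only sample size inflation is 10% for loss to follow-up.

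**The concern.** An exclusion criterion normally decides who may be randomised. This one cannot, because the fact it depends on does not yet exist at randomisation. If it is applied afterwards, the patients followed and analysed are no longer the patients randomised, and the protection that randomisation gives against selection is lost for that part of the sample.

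Two features make this more than a matter of wording. First, the arms already differ during the procedure: the loading drugs differ, and peri-procedural aspirin is barred in the experimental arm (Intervention). A thrombotic complication during PCI could thus be both an effect of the regimen and a reason to call the PCI unsuccessful. Second, the primary efficacy composite includes MI, stent thrombosis and revascularization (Outcomes), so an exclusion based on the stent result may partly be an exclusion based on the outcome. The result at stake is a non-inferiority test with a margin of 1 percentage point on an expected rate of 2%.

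**Working it through.** **1. Order of events.** Diagnostic angiography, then recruitment and randomisation, then the allocated loading dose, then stent insertion, then the PCI result on which criterion vi depends. All four sections agree on the part before the stent. Criterion vi therefore acts after allocation and after first study drug. An exclusion at that point and an analysis of everyone by allocation cannot both hold.

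**2. The plan's own sample size.** With p = 0.02, margin 0.01, one-sided alpha 5% and power 80%, Formula 1 gives N = 2 × ((1.645 + 0.842)/0.01)² × 0.02 × 0.98 = 2423.6, so 2424 per arm, as stated. With 10% loss, 2424/0.90 gives 2694 per arm, or 5388 in total, close to the stated 5400. The point does not turn on these figures.

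**3. Effect on power.** The documents give no rate of unsuccessful PCI, so the shares here and below are assumptions. Removing 1%, 2%, 5% or 10% takes out about 4, 7, 18 or 36 of 360 patients, or 54, 108, 270 or 540 of 5400. With n = 2424 reduced by that share, power = Φ(0.01/√(2 × 0.02 × 0.98/n) − 1.645) is 79.7%, 79.3%, 78.2% or 76.2%. Power is not the main issue.

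**4. Equal exclusion at equal risk.** Assume that removed patients have a 10% event rate and those kept have 2%.

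- 2% removed: full rate 0.98 × 0.02 + 0.02 × 0.10 = 2.16%; share of events lost 0.20/2.16 = 9%.
- 5% removed: full rate 0.95 × 0.02 + 0.05 × 0.10 = 2.40%; share lost 0.50/2.40 = 21%.

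Events are lost in both arms, but the between-arm difference is essentially unchanged.

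**5. Equal exclusion, but risk differs by arm among those removed.** If the risk is 10% in one arm and 20% in the other, the true difference left out of the test is 0.02 × 0.10 = 0.2 points (2% removed) to 0.05 × 0.10 = 0.5 points (5% removed), which is 20% to 50% of the margin.

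**6. Unequal exclusion with no true difference.** Take a true rate of 2% in both arms. One arm removes 3% and the other removes 3% plus an extra share, and removed patients have risk r. The rate among those kept is (0.02 − e × r)/(1 − e), where e is the share removed. For 3% against 4% and r = 10%, this gives 1.753% against 1.667%.

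| Extra share removed | Shift, r = 10% | Shift, r = 20% |
|---|---|---|
| 1 point | 0.09 points | 0.19 points |
| 2 points | 0.17 points | 0.39 points |
| 3 points | 0.26 points | 0.59 points |

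The shift favours whichever arm removes more patients.

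**The case against.** The strongest defence is that no section says these patients leave follow-up or analysis. The protocol twice commits to intention to treat, the article is condensed, and its flow diagram is not available here. Patients who meet criterion vi might stop study drug and still be analysed as allocated. That reading is possible, and it limits the claim: intention to treat is broken if criterion vi is applied as an exclusion, which is its plain meaning in the list. It does not remove the conflict, because nothing in the article states that reading.

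A reader might also infer the following, which the documents do not support:

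- *That someone who knows the arm makes the decision.* The Randomization section does say: "The only person who is involved in randomization is the interventional cardiologist who conducts PCI", and Blinding says that the randomising cardiologist knows the allocation and gives the loading tablets. But criterion vi names the supervising cardiologist, Intervention separates performer from supervisor (for angiography), and Blinding says that the randomising cardiologist takes no part in treatment. The Randomization and Blinding sections conflict on that role, so someone who knows the arm may be present; more than that is not shown.
- *That the bias favours ticagrelor.* Withholding aspirin could produce more procedural thrombosis in the experimental arm. Yet Background and rationale describes ticagrelor as acting faster and more consistently than clopidogrel, which points the other way.
- *That a per-arm loss of events can be set against the margin.* Assuming 2% to 6% removed at 5% to 10% risk gives 0.1 to 0.6 points per arm, but the margin applies to the difference between arms. Likewise, one event among 180 is 0.56 points whatever its cause, and 0.04 points among 2424. At 180 per arm the one-sided 95% half-width is already about 1.645 × √(2 × 0.02 × 0.98/180) = 2.4 points.
- *That these patients carry the highest stent risk.* This is plausible, but the article gives no event rate for them.

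**Conclusion.** The point stands as a conflict between the eligibility rule and the stated order of randomisation, with a direct consequence for the analysis set. Applied as written, criterion vi is a subjective post-randomisation exclusion on a procedural result that treatment may affect and that overlaps with the primary endpoint.

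The size of any bias cannot be derived from the documents, and its direction is open. The illustrative shifts of roughly 0.1 to 0.6 points rest entirely on assumed exclusion shares and event risks. They show only that unequal exclusion, or unequal risk among those excluded, can matter against a 1-point margin. Equal exclusion at equal risk mainly costs events and a little power. The documents do not establish that patients will in fact be dropped from the analysis, that an unblinded person will drop them, or that the result would be tilted towards ticagrelor.

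**What to change.** Reconcile exclusion vi with the Intervention, Participant timeline, Randomization and Blinding sections, so that only criteria assessable before randomisation exclude a patient from the trial population. In Statistical analysis, state that every randomised patient is followed and analysed by allocation whatever the PCI result. Record procedural success as a variable, report the number of criterion vi cases by arm, and use the restriction to successful PCI only as a supportive analysis. How study treatment is managed after an unsuccessful PCI is for the investigators to decide; staying in follow-up and in the analysis need not depend on it.

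The cost is amendment wording. A few patients with unsuccessful or suboptimal PCI stay in the analysis, which may raise the event rate slightly. By the dates under Trial status, recruitment to the initial phase was due to end on December 1, 2024, so new eligibility wording may come too late for that phase. The analysis rule could still be corrected if outcome data have been kept for these patients, and the Discussion foresees possible continuation to the full sample, where both changes would apply.
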